### Recruitment {20}

A total of 36 male, female, and diverse individuals with CAI are recruited in and around Krefeld, Germany. Recruitment is done through flyers posted at the university and cooperation partners, social media postings, and word of mouth. In addition, sports clubs and groups of different sports (e.g., soccer, handball, basketball, tennis, running), rehabilitation centers, physiotherapy and medical practices, and hospitals are contacted via email and personal visits to inform them about the study.

## Assignment of interventions: randomization

### Sequence generation: who will generate the sequence {21a}

Sequence generation is performed by physiotherapist AB with the two student assistants RK and CB. Permuted block randomization is performed using the program DatInf RandList version 1.5 (Tübingen, Germany).

### Sequence generation: type of randomization {21b}

A permuted block randomization with blocks of 6 is performed using the program DatInf RandList version 1.5 (Tübingen, Germany). Participants are randomly assigned to either the control, Mini Stability Trainer (intervention), or Wobble Smart Board (comparison) groups with an allocation ratio of 1:1:1 (12 for control, 12 for Mini Stability Trainer, and 12 for Wobble Smart Board groups). Assignment of interventions is completed after the initial measurement using sequentially numbered, opaque, sealed envelopes to ensure no interference with group assignment. One physiotherapist (AB) and two occupational therapists (RK, CB) independently generate the allocation sequence, enroll participants, and assign participants to interventions.

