### Trial design {12}

This study protocol follows the “Standard Protocol Items: Recommendations for Interventional Trials (SPIRIT) 2013 Statement” (https://www.equator-network.org/reporting-guidelines/spirit-2013-statement-defining-standard-protocol-items-for-clinical-trials/). The study is a prospective, single-center, interventional, randomized controlled trial with an intervention group (forefoot and rearfoot stability training) and two comparison groups, either a usual balance training group or a control group. It is a single-blind (principal investigator) design with patients randomized 1:1:1 to one of the three parallel groups. To ensure internal validity, a control group is included that does not receive any balance training intervention. Because many patients with CAI do not seek medical or physical therapy and continue with their usual activities, participants in the control group are allowed to do so. A summary of study information is presented in Table 1.

**Table 1 Tab1:** Study information

Category	Information
Country	Germany
Intervention	Active part: 6 weeks of training with the Mini Stability Trainer according to a predefined exercise schedule; 6 weeks of training with the Wobble Smart Board according to a predefined exercise schedule; one training session is performed under the supervision of a member of the study team, at least 17 training sessions are performed independently by each subject at home Control group: activities of daily living and sports activities; balance exercises are not allowed
Inclusion and exclusion criteria	Inclusion criteria: age between 18 and 44 years; based on the guidelines of the International Ankle Consortium: history of at least one ankle injury more than 1 year ago with typical signs of inflammation; self-reported ankle instability; in addition, two or more episodes of “giving way” must have occurred within the previous 6 months; Cumberland Ankle Instability Tool (CAIT ^a^) score ≤ 24 (in the case of bilateral ankle instability, the more severely affected side is selected) Exclusion criteria: acute injury, surgery or fracture of the lower extremity, neurological disorders, chronic overuse injuries such as Achilles or patellar tendinopathy; current participation in a targeted ankle rehabilitation program

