### Participant timeline {18}

After a potential participant has contacted the study staff (AB) via email, the participant receives a self-administered questionnaire asking for basic socio-demographic and injury-related data and the CAIT to complete the initial eligibility screening. If the participant meets the eligibility criteria, an appointment is made for the first measurement in the laboratory. At the first appointment, all eligibility criteria are finalized and the participant is enrolled after providing informed consent. Outcome measures are then completed and the participant is assigned to one of the three groups by closed envelope. At the second appointment after the 6-week intervention, outcome measures are repeated. At the 4-week and 12-week follow-up visits, participants are contacted by email and asked to complete the FAAM questionnaire. A detailed description of the study procedure can be found in Table 6.

**Table 6 Tab6:** Study procedure

Time point	Investigation period				
	Entry	Baseline	According to the group categorization		
	<2 weeks	Time = 0 or preliminary examination and group classification	Intervention (6 weeks)	After the intervention	4 and 12 weeks after the intervention
Entry: Questionnaires	x				
Assignment		x			
Intervention					
Group 1: control			x		
Group 2: Mini Stability Trainer			x		
Group 3: Wobble Smart Board			x		
Assessments					
CAIT ^a^		x			
FAAM ^b^		x		x	x
YBT ^c^		x		x	
MBESS ^d^		x		x	
3D-Gait analysis		x		x	

^a^CAIT, Cumberland Ankle Instability Tool, ^b^
*FAAM *Foot and Ankle Ability Measure, ^c^*YBT *Y-Balance Test, ^d^*MBESS *Modified Balance Error System

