### Sample size {19}

An a priori sample size estimation based on the results of pilot measurements [40] examining change in dynamic balance after 6 weeks of balance training using the Mini Stability Trainer indicated that 33 participants (11 per group) would be needed to detect a mean difference of 4.6% in the composite score of the YBT with an effect size of *f* = 0.33 and a probability of 1 − *β* = 0.9 at a significance level of *α* = 0.05. To account for potential dropouts and loss to follow-up, the target number of participants is 36 (12 per group).

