## Assignment of interventions: blinding

### Who will be blinded {24a}

Since the interventions are performed by the participants, they are visible to them. Therefore, it is not possible to blind participants to the intervention. However, participants in the intervention groups are not told which intervention is being studied and which is the comparison. It is not possible to blind participants in the control group. The observer performing the measurements assigns participants to groups using sealed envelopes after the baseline measurements and is therefore blinded to group assignment at baseline but is not blinded to group assignment at post-measurement and follow-up. In this way, participants are also blinded and uninfluenced by the group assignment at baseline, and possible biases or expectations will not affect the results. The principal investigator who analyzes the data is blinded to group allocation throughout the study.

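### One fixed block size of 6 in an open, single-centre trial makes about one assignment in five certain before its envelope is opened, so blinding at baseline is not secured for those participants

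*Protocol article*

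**What the plan says.** Sequence generation {21b} fixes a single block size: "A permuted block randomization with blocks of 6 is performed". The ratio is 1:1:1, with 12 participants per arm and 36 in total. Trial design {12} describes one site: "The study is a prospective, single-center, interventional, randomized controlled trial". Items {21a} to {23} name no stratification factor, so one list runs in order of enrolment.

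Allocations are open once made. On participants, {24a} says: "Therefore, it is not possible to blind participants to the intervention". The observer who measures also assigns by envelope after the baseline tests and, in the words of {24a}, "is therefore blinded to group assignment at baseline but is not blinded to group assignment at post-measurement and follow-up". The timeline {18} places the final eligibility decision at that same visit: "At the first appointment, all eligibility criteria are finalized and the participant is enrolled after providing informed consent". The outcome measures follow, and then the envelope.

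Three further statements matter:
- {21a} and {21b} have the same physiotherapist and two assistants generate the sequence, enrol and assign.
- {22} says that only the participant opens the envelope.
- {23} gives the physiotherapist and the principal investigator access to the sequence file.

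**The concern.** The only support that {24a} gives for blinding at baseline is that the envelope is opened after the measurements. That protects the baseline only if the next arm cannot be worked out beforehand. With one constant block size, one list and visible past allocations, the end of each block can be worked out by counting, however opaque the envelopes are.

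Foreknowledge could act at two points before the envelope. One is enrolment: entry rests partly on self-reported instability and episodes of giving way, and staff decide whom to book next. The other is baseline scoring: the MBESS is an error count made by the assessor. Both primary outcomes are compared as change from baseline, so a shift in baseline scores or case mix that depends on the coming arm would feed into the between-group comparison. No adjusted analysis is planned ({27d}).

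**Working it through.** **Inputs.** Block size 6 and ratio 1:1:1 ({21b}); 36 participants ({19}); one centre ({12}); no stratification named ({21a} to {23}). The calculation assumes that the enrolling team keeps track of all earlier allocations, knows the block size and does not consult the list.

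**The plan's own figure.** 36 / 6 = 6 complete blocks, and 6 × 2 = 12 per arm. This agrees with the stated 12/12/12. The protocol gives no figure for predictability.

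**Enumeration.** A block with two places for each of three arms has 6! / (2! 2! 2!) = 90 equally likely orders. At each place, count the orders in which the arms already used determine the next one.

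- The 6th place is always the one left over, so its probability is 1.
- The 5th place is certain only if the last two places are the same arm: 3 × 4! / (2! 2!) = 18 orders, and 18 / 90 = 1/5.
- The 1st to 4th places are never certain.

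| Place in block | 1 | 2 | 3 | 4 | 5 | 6 | Mean | Of 36 |
|---|---|---|---|---|---|---|---|---|
| Next arm certain | 0 | 0 | 0 | 0 | 1/5 | 1 | 20.0% | 7.2 |
| Exactly one arm ruled out | 0 | 0 | 1/5 | 3/5 | 4/5 | 0 | 26.7% | 9.6 |
| Control versus training certain | 0 | 0 | 1/15 | 1/5 | 7/15 | 1 | 28.9% | 10.4 |
| Best guess correct | 0.333 | 0.400 | 0.500 | 0.533 | 0.600 | 1.000 | 56.1% | 20.2 |

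Certain assignments: (1/5 + 1) / 6 = 0.20, and 0.20 × 36 = 7.2 expected. At least 6 are certain, one per block. At least one arm is excluded in 20.0% + 26.7% = 46.7% of assignments. The best guess compares with 33.3% by chance.

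**Varying block sizes.** An optimal guesser who knows the set of sizes but not their order, and has no access to the list, was simulated over 36 assignments:

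| Block sizes | Known with certainty | Best guess correct |
|---|---|---|
| 6 only | 20% | 56% |
| 3, 6, 9 | about 3.5% | about 55% |
| 6, 9, 12 | about 2.5% | about 52% |

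The gain is almost all in removing certain knowledge.

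**With access to the list.** For someone who can open the file, up to 36 of 36 assignments are knowable whatever the block size.

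**The case against.** The strongest objection is that block size is not the main weakness. The people who enrol and assign also generate the sequence, and the enrolling physiotherapist can open the file, so changing block sizes alone would leave them just as well informed. This stands, and it determines the remedy. It does not remove the point: restricting access to the list would still leave the 20% that counting reveals.

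Other objections stand in part:
- Blocks of 6 give exactly 12/12/12 and contradict nothing as a design choice. What fails is the blinding statement that rests on them.
- The effect on the result may be modest. If only certain slots were affected, a baseline scoring shift of b in 20% of an arm moves its mean by 0.2 × b. An illustrative 5-point YBT shift gives 0.2 × 5 = 1.0 point, against the planned difference of 4.6% in {19}. Opposite shifts in two arms would double this, and acting on partial guesses would add to it. YBT reach is read from a tape in 5 mm steps, which limits discretion; MBESS error counting is more exposed.
- The post-intervention assessor is openly unblinded for every participant, which is a larger route to bias in the change score.
- Slow accrual limits the choice of whom to book into a slot.

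A reader might infer that staff open the envelopes. {22} says that the participant does. This changes no figure, because staff see each result when they assign and when they deliver the supervised session.

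**Conclusion.** The point holds as a weakness in a stated safeguard. Counting alone makes 20% of assignments (7.2 of 36 expected, at least 6) certain before the envelope is opened, so {24a} does not secure blinding at baseline for those participants. The figure assumes that staff follow earlier allocations across the team. It is a lower bound, since {23} also gives the enrolling physiotherapist the whole list.

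A reader might go further and conclude that enrolment was steered or baseline scores were shifted. The documents do not support that: they show an opportunity, with no evidence that anyone used it, and the size of any effect on the primary comparisons cannot be derived from them. Nor do they show that blinding at baseline failed for every participant. The change is worth making because it is cheap and removes an avoidable risk.

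**What to change.** 1. **Unopened envelopes.** Replace the fixed block of 6 in {21b} with permuted blocks of randomly varying size, for example 3, 6 and 9, keeping 1:1:1 and the sealed envelopes. The list should be generated and held by a person who does not book, screen, measure or assign participants; an existing team member withdrawn from those tasks would do. Block sizes should not be disclosed to the others.
2. **File access.** Remove the enrolling physiotherapist's access in {23}. Without steps 1 and 2 together, varying the block size gains nothing.
3. **Statement in {24a}.** Say that blinding at baseline was not assured under fixed blocks of 6. This applies however many envelopes remain.
4. **Participants already allocated (optional).** Add one sensitivity analysis of YBT and MBESS that leaves out only those whose arm was determined by earlier allocations: all 6th places, and a 5th place only where both remaining places were the same arm. About 7.2 of 36 would be excluded, against 12 if every 5th and 6th place were dropped. It lowers precision, breaks the 12/12/12 balance and cannot detect steering in other slots. {27a} and {27d} say that no additional analyses are planned, so they would need a matching edit.

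**Cost.** A new list for the remaining envelopes and a short amendment notified to the ethics committee and registry, as {31} already provides. Arm sizes may end one or two away from 12 if recruitment stops inside a block. Recruitment began in July 2023 and was expected to finish by January 2026, so steps 1 and 2 may reach few participants. The best-guess rate would fall only to about 52–55%; the benefit is the drop in certain knowledge from 20% to about 2–3.5%.

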### Allocation concealment mechanism {22}

Once randomization is complete, the group assignments are placed in opaque, sealed envelopes. The envelopes are numbered and opened exclusively by the respective participant to ensure blinding until allocation.

### Implementation {23}

The physiotherapist AB and the principal investigator MA have access to the random allocation sequence. Access to the file is dependent on the verification of the file with the user’s personal password.

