Study type	Allocation: randomized; model: parallel allocation; intervention description: comparison of clinical outcome measures at four time points between three cohorts (Wobble Smart Board, Mini Stability Trainer, control group) of subjects with chronic ankle instability (CAI ^b^), whether the two intervention groups reduce the primary and secondary outcome measures compared to the control group; blinding: single-blind; blinding description: the principal investigator analyzing the results will be blinded to group allocation; different investigators will be used to perform the intervention and to analyze the results
Primary outcomes	Dynamic balance and postural stability using the Y-Balance Test (YBT ^c^) and Modified Balance Error Scoring System (MBESS d)
Secondary outcomes	Gait biomechanics using 3D gait analysis (e.g., ankle abduction and adduction; knee varus/valgus position; spatiotemporal parameters); ankle function using the Foot and Ankle Ability Measure (FAAM ^e^)

^a^*CAIT *Cumberland Ankle Instability Tool; ^b^*CAI *chronic ankle instability; ^c^*YBT *Y-Balance test; ^d^*MBESS *Modified Balance Error Scoring System; ^e^*FAAM *Foot and Ankle Ability Measure

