### How will be blinding be achieved {24b}

The blinded principal investigator is unaware of the group allocation of participants because the envelopes are sealed and inaccessible to him.

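### The analysing principal investigator is called blinded but has access to the allocation list, and the staff who make the list also recruit, so neither analyst blinding nor concealment is assured as written

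*Protocol article*

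**What the plan says.** All references are to the protocol article.

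**Blinding of the analyst.** Trial design {12} describes the trial as single-blind, with the principal investigator as the blinded party, and its Table 1 adds that "the principal investigator analyzing the results will be blinded to group allocation". Item {24a} extends this to the whole trial: "The principal investigator who analyzes the data is blinded to group allocation throughout the study". Item {24b} gives the mechanism: the principal investigator "is unaware of the group allocation of participants because the envelopes are sealed and inaccessible to him". Item {3d} again calls this person blinded and has them monitor and analyse all data.

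**Access to the list.** Implementation {23} states that the physiotherapist and the principal investigator "have access to the random allocation sequence", and continues: "Access to the file is dependent on the verification of the file with the user’s personal password".

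**Who makes the list and who recruits.** Item {21a} has the physiotherapist and two assistants generate the sequence. Item {21b} says that one physiotherapist and two colleagues "independently generate the allocation sequence, enroll participants, and assign participants to interventions". The physiotherapist is also the first contact for screening ({18}), takes consent ({32a}) and gives the supervised training session ({15a}).

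**Stated safeguards.** The envelopes are numbered, opaque and sealed ({21b}). Only the participant opens them ({22}), and only after the baseline measurements ({18}, {24a}). The list file is password-protected ({23}).

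**The concern.** Two protections are described in a way that the protocol's own text undercuts.

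The first is blinded analysis. Important analytic choices are still open. Item {27a} names the tests only provisionally (repeated-measures ANOVA, Friedman or Kruskal-Wallis), and {27c} leaves single or multiple imputation to be chosen once data collection is over. Blinding the analyst is what would keep those choices free of the results by arm. If the analyst can open the list, that protection depends on restraint and not on procedure.

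The second is concealment. If a recruiter can know the next allocation, decisions on eligibility and on the timing of enrolment can be affected, as can scoring at baseline. Both primary outcomes involve judgement: the MBESS is an error count, and each YBT attempt must be ruled valid or invalid. With 12 participants per group, a few selectively placed participants could matter.

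**Working it through.** The point rests on text, so the statements are set side by side first. The plan gives no figure of its own to reproduce.

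**1. Analyst blinding**
- Premise A ({23}): the principal investigator has access to the sequence, using a personal password.
- Premise B ({12}, {24a}, {3d}): the principal investigator analyses the data and is blinded, according to {24a} for the whole trial.
- Reason given for B ({24b}): the envelopes are out of reach.
- The envelopes are filled from the sequence. Someone who can read the sequence does not need the envelopes. The password keeps others out but admits this person. The reason in {24b} therefore does not support B while A stands, and no other item limits A, for example to the time after analysis.

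**2. Concealment from the recruiter**
- Generate, enrol and assign: the same three staff ({21b}; generation confirmed in {21a}).
- Continuing access to the list: the physiotherapist ({23}), who also screens ({18}) and takes consent ({32a}).
- Claimed result: the observer is blind to group at baseline ({24a}).
- Sealing an envelope hides its content from someone who does not know the order. It does not hide it from someone who generated the order or can look it up. The word used in {21b} for how the three staff work, whether it means independent of each other or of the principal investigator, does not separate generation from enrolment on either reading.

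**3. How predictable the next allocation is**

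Inputs: three arms at 1:1:1, fixed blocks of 6 and 36 participants ({21b}), hence 36/6 = 6 blocks with two places per arm in each.

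*With the list:* 36 of 36 allocations can be known.

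*Without the list*, assuming that the person knows the block size and the earlier allocations, the chance that the best guess is right at each position in a block is:
- Position 1: 1/3
- Position 2: 2/5
- Position 3: 1/2 (the largest remaining share is 2 of 4 in every case)
- Position 4: the three remaining places are all different with probability 2/5, otherwise split 2 and 1, so 2/5 × 1/3 + 3/5 × 2/3 = 8/15
- Position 5: the two remaining places are the same arm with probability 1/5, so 1/5 × 1 + 4/5 × 1/2 = 3/5
- Position 6: 1

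Sum: 1/3 + 2/5 + 1/2 + 8/15 + 3/5 + 1 = 3.37 correct per block, and 3.37/6 = 56%, against 33% by chance.

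Allocations known with certainty: (1/5 + 1)/6 = 20%, which is 0.20 × 36 = 7.2 participants on average.

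These figures are secondary. They show what remains predictable after list access is removed. They measure predictability, not bias in the YBT or MBESS.

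**The case against.** The safeguards are real. Numbered opaque envelopes that only the participant opens after baseline, together with a password on the file, are more than many small trials describe. Access is also not use: nothing says that the principal investigator or the physiotherapist consulted the list. Part of eligibility, including the CAIT, is collected by self-completed questionnaire before the first visit ({18}), which narrows the room for selective enrolment without closing it. All of this stands. It limits the conclusion to protections that are not assured. A reader might infer that blinding and concealment have failed, or that the envelopes hide nothing from anyone; the documents support neither.

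Some role attributions are inferences. Item {18} does not say who finalises eligibility. That the physiotherapist is the observer follows from reading {24a} together with {3d}, where the physiotherapist is named as the assessor. The concealment point does not need either inference, because the list access and the recruiting role are stated. The baseline-blinding point does rest on the observer being one of the staff who generate or can open the list. Item {24a} says that the observer assigns participants, which under {21b} is a task of those same staff.

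A reader might also count the observer who "is not blinded to group assignment at post-measurement and follow-up" as part of the error. That is an openly declared limitation of the design and contradicts nothing. Nor is analyst blinding the only blinding claimed: {24a} also describes blinding at baseline and says that trained participants are not told which device is under study.

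**Conclusion.** The concern holds in this form. Item {23} contradicts {12}, {24a}, {24b} and {3d} on whether the analysing principal investigator can learn the allocation, and nothing in the article resolves it. The single-blind label is therefore not assured as written. Separately, {21a}, {21b} and {23} do not separate making or holding the list from recruiting, so concealment from the recruiter and the observer's claimed blinding at baseline are not assured.

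For a list holder the size is complete knowledge of all 36 allocations. For staff without the list it is 20% certain and 56% guessable, given knowledge of the block size and past allocations. The resulting bias in the outcomes cannot be computed from the documents, and no breach is shown. The contradiction should be corrected before the analysis begins, because the choices of test and imputation are still open.

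**What to change.** 1. Withdraw the principal investigator's access to the list. Supply an analysis dataset with groups coded A, B and C and without fields that reveal the arm, such as training-booklet entries. Break the code only when the analysis is final. If the principal investigator has already opened the list, drop the claim of blinded analysis instead.
2. Withdraw the recruiting physiotherapist's access. For slots not yet used, have a new list generated and held by someone with no part in enrolment, assessment or analysis.
3. Reconcile {12} (Table 1), {21a}, {21b}, {23}, {24a}, {24b} and {3d}. In passing, settle the different descriptions of the two co-workers in {21a} and {21b}.
4. Report who had access to the list, from when to when, and how many participants were allocated under the present arrangement.

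A change of post-test rater is not part of this fix. The article does not show that another trained rater unaware of allocation is available. For participants already measured at baseline, a new rater would add between-rater error to the change score, and the article quotes MBESS reliability of only 0.6–0.88.

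Cost: a password change, a coded export and a short amendment notified to the ethics committee and registry ({31}). The new list needs a small amount of time from one uninvolved person, and the article does not show that the present team includes one. Enrolment began in July 2023 and was expected to finish by January 2026, so few slots may remain and item 2 may protect little. Items 1, 3 and 4 keep their value after recruitment closes.
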